### Statistical analysis

The Research Electronic Data Capture (REDCap) platform will be used for data entry and storage. Continuous variables will be reported as mean ± standard deviation (SD) for normally distributed data, or as median and interquartile range (IQR, 25th–75th percentile) for non-normally distributed data. Categorical variables will be presented as absolute numbers and percentages. Normality will be assessed using the Shapiro–Wilk test. For within-participant comparisons between TEPNS and TDES conditions, paired t-tests will be used for normally distributed data, and the Wilcoxon signed-rank test will be applied for non-parametric data. The primary analysis will be performed using a linear mixed-effects model appropriate for a two-period crossover design, including treatment, period, and sequence as fixed effects, and participant as a random effect, thereby accounting for within-subject correlation. Percentage changes in diaphragm thickness, thickening fraction, and mobility will also be calculated.

The frequency of adverse events will be systematically recorded and descriptively analyzed to characterize the safety profile of both interventions. Additionally, associations between diaphragm thickness, thickening fraction, diaphragmatic mobility, stimulation intensity, participant-reported discomfort, and the occurrence of adverse events will be explored using Pearson’s or Spearman’s correlation coefficients, as appropriate. Adjustment for multiple comparisons will be performed where applicable to control the risk of type I error. Missing data will be addressed using multiple imputation by chained equations under the missing-at-random assumption. Each imputed dataset will be analyzed separately, and the results will be pooled using Rubin’s rules to obtain valid statistical inferences.

All statistical analyses will be performed using the Statistical Package for the Social Sciences (SPSS) version 28.0.1 (SPSS Inc., Chicago, IL, USA). A two-sided p-value < 0.05 will be considered statistically significant. The statistician responsible for data analysis will be blinded to the allocation sequence and intervention timing.

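### A normality-gated paired t/Wilcoxon test with no period term and no stated role stands beside the primary crossover model, and the statistician's blinding, read literally, conflicts with that model's inputs

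*Protocol article*

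**What the plan says.** All the relevant sentences are in the protocol article, Statistical analysis, unless another section is named.

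- **Paired tests.** For within-participant comparisons of the two conditions, "paired t-tests will be used for normally distributed data, and the Wilcoxon signed-rank test will be applied for non-parametric data". The check that separates the branches is given as "Normality will be assessed using the Shapiro–Wilk test". The text does not limit these tests to particular outcomes or call them supportive.
- **Primary analysis.** The next sentence reads: "The primary analysis will be performed using a linear mixed-effects model appropriate for a two-period crossover design". Its fixed effects are treatment, period and sequence, with a random effect for participant. It does not list the outcomes it covers.
- **Blinding of the analyst.** "The statistician responsible for data analysis will be blinded to the allocation sequence and intervention timing". No coding of the analysis dataset is described. The Blinding section mentions coded names only for the ultrasound files.
- **Sizing.** The Sample size section uses diaphragm thickness and a paired t-test framework, with two-sided 5% significance, 80% power and about 20% dropout. It plans a pilot of 12 and states no final sample size.
- **Allocation.** The Randomization and allocation section gives 1:1 allocation to order, in blocks of 4, balanced over three age groups.

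**The concern.** Two different procedures are stated for one contrast. The mixed model removes any systematic difference between the first and second stimulation session; the paired t-test and the signed-rank test do not. The primary label settles which governs the primary analysis. It does not settle which governs discomfort or any other outcome outside that analysis, and it does not say what a paired result means if it differs from the model.

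A period effect cannot be ruled out: the two sessions are separated by a one-hour washout, and intensity is set to each participant's tolerance in each session. If there is one, the paired tests lose power when the sequences are equal in size and give a biased estimate when they are not.

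The second issue is the blinding sentence. Period and sequence are two of the three fixed effects in the primary model. An analyst who does not hold those columns cannot fit it as specified.

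**Working it through.** The article states no effect size, SD or final N, so there is no planned figure to reproduce. The inputs below marked *assumed* are not in the document.

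**Inputs.** Two-sided 5% and 80% power (Sample size). SD of the within-participant difference set to 1. Treatment effect 0.5 SD (*assumed*). Period effect π of 0, 0.3 or 0.5 SD (*assumed*). 34 completers, which is what a paired t-test needs for 80% power at 0.5 SD; with 20% dropout, 34/0.8 = 42.5, so 43 recruited.

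**1. Balanced sequences, 17+17.** Write each participant's TEPNS minus TDES difference as D = τ + π in one order and τ − π in the other. The period terms cancel in the mean, so the paired estimate is unbiased. They remain in the sample variance, which has expectation 1 + π²·N/(N−1):

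- π = 0.3: 1 + 0.09 × 34/33 = 1.093, so the standard error is overstated by a factor √1.093 = 1.045.
- π = 0.5: 1 + 0.25 × 34/33 = 1.258, so the factor is √1.258 = 1.121.

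Simulated power (200,000 runs per setting):

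| Period effect (SD) | Paired t | Crossover model |
|---|---|---|
| 0 | 81% | 81% |
| 0.3 | 78% | 81% |
| 0.5 | 74% | 81% |

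A separate simulation of the full gated procedure (Shapiro–Wilk at 0.05 on the differences, then paired t or Wilcoxon; 5,000 runs) also gives 74% at 0.5 SD.

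**2. Unequal sequences.** The mean of D becomes τ + π(n1 − n2)/N. At 7:5 the bias is π × 2/12 = π/6, which is 0.05 SD for π = 0.3 and 0.083 SD for π = 0.5. The simulated means agree (0.050 and 0.083). The crossover model averages the two sequence means with equal weight, so π cancels. The 7:5 split is an illustration at the pilot size of 12; incomplete blocks within age groups and dropout could each produce such a split.

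**3. If either test could support a claim.** Simulated type I error for significance on the model or the gated test, with period effects of 0 to 1 SD, is 4.5–5.7% with balanced sequences, 4.5–6.3% at 14:10, 6.0–7.0% at 23:17 and 6.5–8.0% at 8:4. The model alone stays at 4.3–5.7% throughout.

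**4. Blinding against the model.** In a simulated 12-participant example:

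- Full model: estimate 0.643, p = 0.0560.
- Treatment labels swapped, real period and sequence kept: estimate −0.643, p = 0.0560.
- Period and sequence removed: p = 0.0975, identical to the paired t-test.

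Masking what the treatment codes mean therefore costs nothing. Withholding period and sequence turns the primary model into the paired t-test.

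**The case against.** The strongest reply is that the primary inference is already protected. The mixed model is named primary, it adjusts for period, and the power loss and bias above belong to a test that is not primary. This stands. A reader might infer that Shapiro–Wilk decides between the paired test and the model. It does not: it only chooses between paired t and Wilcoxon.

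A second reply is that being blinded to sequence and timing may mean only that the analyst is not told which order began with TEPNS. This is a fair reading, and under coded labels the model runs with an identical p-value. A reader might infer that only the paired tests could be run; the wording is ambiguous and does not establish that.

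Third, the 0.3–0.5 SD period effect is not in the document. That is correct, and it is used here only as an assumed range.

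Two further inferences are not supported. One is that the exploratory correlations ignore clustering: the article does not say that repeated rows per participant are pooled. The other is that the signed-rank branch defeats multiple imputation: a Hodges–Lehmann estimate and interval accompany that test, and the pooling step works for the primary model.

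What remains is that the paired tests are stated for the same contrast without a role, and that the blinding sentence does not fit the model's terms as written.

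**Conclusion.** The concern holds in a limited form. The article states a period-free, normality-gated test for the TEPNS–TDES comparison alongside the crossover model and leaves its role open, which matters most for outcomes that the primary analysis may not cover, such as discomfort. The cost of using the paired t-test is about 3 to 7 percentage points of power with balanced sequences (about 81% to 78–74%), and a bias of period effect × (n1 − n2)/N with unequal ones. Both figures rest on an assumed period effect of 0.3–0.5 SD; the power figures also assume 34 completers and a 0.5 SD treatment effect. With no period effect there is no power loss and no bias. Inflation of type I error, if either test may be claimed, is small to moderate and arises with unequal sequences.

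The blinding sentence is a conflict of wording to reconcile, not evidence that the primary model cannot be fitted. The change is worth making because the better method is already in the plan.

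**What to change.** 1. State that the crossover mixed model (treatment, period, sequence, random participant) is the sole inferential test of TEPNS against TDES for thickness, thickening fraction, mobility and discomfort.
2. Delete the Shapiro–Wilk-gated paired t and Wilcoxon tests for this contrast, or label them sensitivity analyses only.
3. For discomfort, name as the sensitivity analysis a rank test that respects period, for example a rank-sum comparison of within-participant period differences between the two sequences. A log scale will not do, because the score can be 0.
4. Reword the blinding sentence: the statistician receives period and sequence with treatments coded A and B, and is masked only to what A and B mean.

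The cost is a few sentences in the Statistical analysis section. No visit, measurement or sample size changes. The article reports that recruitment is under way with no results yet, so the change can be made before any analysis.

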### Transcutaneous electrical phrenic nerve stimulation (TEPNS)

The TEPNS parameters will be biphasic waves with a frequency of 10 Hz, a pulse width 200 μs, a rise time of 1.0 second, “on” and “fall” times of 1.0 second each, and a 2-second “off” time, resulting in 12 stimuli per minute [19]. TEPNS application will begin by identifying the right cervical phrenic nerve pathway using ultrasound, guided by anatomical landmarks including the anterior scalene muscle, sternocleidomastoid, internal jugular vein, and brachial plexus roots. The phrenic nerve appears as a hypoechoic (darker on ultrasound image), oval structure superficial to the anterior scalene muscle [20]. The active electrode (negative pole) will be placed along the nerve pathway between the heads of the sternocleidomastoid muscle using a 2 mm spherical microcurrent electrode (Neurodyn Esthetic, IBRAMED) (**Fig 3A and 3B**). The passive electrode (positive pole) will be positioned at the acromion shoulder to complete the electrical circuit [21] (**Fig 3C**). Stimulation intensity will be adjusted to the maximum level tolerated by the participant, sufficient to produce a diaphragmatic contraction confirmed by the ultrasound assessment without inducing contraction of the cervical or shoulder muscles [21].

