### Transcutaneous diaphragmatic electrical stimulation (TDES)

The electrical parameters for TDES consist of biphasic waveform with a stimulation frequency of 30 Hz, a pulse width of 400 μs, a rise time of 1.0 second, an “on” time of 1.0 second, a fall time of 1.0 second, and an “off” time of 2 seconds, resulting in 12 stimuli per minute [19]. For TDES application, two self-adhesive electrodes (5.0 x 5.0 cm) will be placed bilaterally in the parasternal region, positioned inferior and lateral to the xiphoid process. An additional pair of electrodes will be placed bilaterally in the intercostal space between the 6th and 7th ribs, along the midaxillary line (**Fig 3D**). Electrode positioning will be guided by an initial ultrasound evaluation to identify the region of greatest visible diaphragmatic apposition. The stimulation intensity, measured in milliamperes (mA), will be gradually increased to the maximum level tolerated by the participant, until visible diaphragmatic contraction is achieved without concomitant contraction of abdominal muscles.

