#### Sensory discomfort evaluation.

Sensory discomfort will be assessed using a horizontal numeric discomfort rating scale. The scale will be presented in printed form on standard 10.0 cm paper, where “0” indicates no discomfort and “10” represents the worst imaginable discomfort. Participants will be asked to rate their perceived sensory discomfort for both interventions (i.e., TEPNS and TDES) at three time points: (i) Baseline – before the start of the intervention; (ii) Measure 5 – the first re-evaluation, conducted between the 4th and 5th minute of the intervention; and (iii) Measure 10 – the final re-evaluation, conducted during the last minute of the intervention [27].

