### Safety assessment

Safety criteria will be evaluated by monitoring for adverse events during the intervention period. Criteria for adverse events include: mean arterial pressure < 65 mmHg, heart rate > 140 bpm or < 50 bpm, occurrence of arrhythmias, oxygen saturation < 92%, elevated body temperature (> 37.7°C), reported discomfort > 7 on the visual analog discomfort scale, and burns or skin injury at the electrode application site. Participants’ vital signs will be continuously monitored throughout the intervention and recorded at 2-minute intervals using a multiparameter monitor (General Electric CARESCAPE Monitor B650).

All adverse events will be recorded and classified according to the World Health Organization’s patient safety guidelines [28], which ranges from “No harm” (no symptoms detected or observed, no treatment required) to “Death” (event caused or significantly contributed to short-term mortality). Adverse events will be monitored only during the intervention, as no long-term side effects related to transcutaneous electrical stimulation have been reported in the literature. Any adverse events will be documented, classified, and reported to the institutional authorities responsible for ethical oversight and study approval.

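### Discomfort above 7 is itself an adverse event, so the planned correlation of discomfort with adverse events is partly built in (minor, exploratory analysis only)

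*Protocol article*

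**What the plan says.** Three parts of the protocol article bear on this.

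- **Sensory discomfort evaluation.** Discomfort is rated from 0 to 10, "where “0” indicates no discomfort and “10” represents the worst imaginable discomfort". The ratings are repeated within each condition: "Participants will be asked to rate their perceived sensory discomfort for both interventions (i.e., TEPNS and TDES) at three time points".
- **Safety assessment.** The adverse-event criteria combine vital-sign limits and arrhythmia with "reported discomfort > 7 on the visual analog discomfort scale, and burns or skin injury at the electrode application site". This section calls the scale visual analog and the previous one calls it numeric. Only one discomfort scale is described, so both must mean the same rating.
- **Statistical analysis.** Diaphragm thickness, thickening fraction and mobility are listed together with intensity, discomfort and adverse events: "stimulation intensity, participant-reported discomfort, and the occurrence of adverse events will be explored using" "Pearson’s or Spearman’s correlation coefficients, as appropriate". No event type is excluded. The frequency of adverse events is separately to be described for both interventions.

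The two intervention sections set intensity by tolerance. For TEPNS, "Stimulation intensity will be adjusted to the maximum level tolerated by the participant". For TDES, it is "gradually increased to the maximum level tolerated by the participant". Both sections add that the diaphragm must contract without neighbouring muscles being recruited.

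**The concern.** One correlated variable is partly a function of the other. A participant who rates discomfort at 8 is an adverse-event case because of that rating, and the correlation then records that a high rating goes with an event. The coefficient cannot distinguish this from what a reader would want to know: whether people who feel more discomfort are also the ones with low saturation, abnormal heart rate, arrhythmia or skin injury.

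Stimulation intensity is affected less directly. It is not part of the event definition, but it is titrated to tolerance, so events defined by discomfort alone can carry the tolerance rule into the intensity association as well.

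Safety and perceived discomfort are secondary objectives in the Abstract, and the Discussion expects the safety data to inform later studies in patients. A reported link between discomfort and adverse events could be read there as a physiological finding when it is partly definitional.

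**Working it through.** The plan states no correlation, discomfort mean or SD, so there is no figure to reproduce. The question is how large a coefficient the definition alone produces when there is no true link.

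**Inputs**

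- From the documents: a 0 to 10 scale, and an adverse event if discomfort > 7 or any other criterion is met.
- Assumed: discomfort *D* is a normal variable rounded to whole numbers and held within 0 to 10. Other events occur with probability *q* = 0.05, independently of *D*. There is one rating per participant, and the same rating is used for the event definition and the correlation.

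**Formulas**

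Let *t* = P(*D* > 7) and let *A* be the adverse-event indicator.

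- P(*A*) = *t* + (1 − *t*)*q*
- Cov(*D*, *A*) = (1 − *q*) × *t* × [E(*D* | *D* > 7) − E(*D*)]
- *r* = Cov(*D*, *A*) / {SD(*D*) × √[P(*A*)(1 − P(*A*))]}

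**Worked case, mean 5, SD 2**

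- *t* = 0.1056, E(*D*) = 5.00, E(*D* | *D* > 7) = 8.495, SD(*D*) = 2.00.
- P(*A*) = 0.1056 + 0.8944 × 0.05 = 0.150, so SD(*A*) = √(0.150 × 0.850) = 0.357.
- Cov = 0.95 × 0.1056 × 3.495 = 0.351.
- *r* = 0.351 / (2.00 × 0.357) = 0.49.

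**Range, *q* = 0.05**

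| Assumed mean (SD) | *t* | E(*D* given > 7) − E(*D*) | SD(*D*) | SD(*A*) | Cov | *r* |
|---|---|---|---|---|---|---|
| 3 (2) | 0.012 | 5.235 | 1.910 | 0.241 | 0.061 | 0.13 |
| 4 (2) | 0.040 | 4.364 | 1.981 | 0.283 | 0.166 | 0.30 |
| 5 (2) | 0.106 | 3.495 | 2.000 | 0.357 | 0.351 | 0.49 |
| 6 (2) | 0.227 | 2.658 | 1.981 | 0.442 | 0.572 | 0.65 |
| 7 (1.5) | 0.369 | 1.570 | 1.500 | 0.490 | 0.551 | 0.75 |

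If *t* = 0, the covariance is zero and so is *r*. More unrelated events dilute the effect. With *q* = 0.15 and mean 5, Cov = 0.85 × 0.1056 × 3.495 = 0.314, P(*A*) = 0.240, SD(*A*) = 0.427, and *r* = 0.314 / (2.00 × 0.427) = 0.37.

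**Check by simulation with Spearman's coefficient**

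This used one row per participant, mean 4 to 6, SD 2, and other events at 5% or 15%. Discomfort was independent of every other criterion. Simulated trials in which the coefficient could not be computed, for example because nobody had an event, were left out.

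| Participants | Mean coefficient | Share with p < 0.05 |
|---|---|---|
| 12 (the pilot size) | 0.15 to 0.64 | 9% to 70% |
| 24 (assumed) | 0.14 to 0.65 | 13% to 93% |
| 40 (assumed) | 0.15 to 0.65 | 18% to 99% |

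With the discomfort criterion removed from the event variable, the mean coefficient lay between −0.01 and 0.01, and 0.6% to 5.3% of tests reached p < 0.05. The association comes from the definition, and removing the overlap removes it.

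**The case against.** The strongest reply is that this is one pair out of 15 (6 × 5 / 2) in an analysis described only as exploratory. Neither the primary mixed model nor the TEPNS–TDES comparison depends on it. That stands, and it sets the severity.

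It can also be said that ratings above 7 may be rare. The intervention sections do not simply push to peak tolerance: avoiding contraction of neighbouring muscles may limit intensity earlier, and no figure in the documents shows that high ratings will be common. This also stands. It is why the range starts at mean 3 and includes zero, but it does not remove the overlap in the definitions.

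Two stronger readings are tempting, and the documents support neither.

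- A reader might infer that each participant enters the correlations twice, once per condition, so that p-values are too small. The protocol does not say that TEPNS and TDES rows are pooled. A correlation within each condition has one row per participant and no such problem, and the row structure is a detail normally left to the analysis plan.
- A reader might infer that the overall event rate will mainly reflect how intensity is set. The protocol plans a descriptive account of adverse events and says they will be documented and classified. It does not say that discomfort events will be merged into one undifferentiated count.

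**Conclusion.** The point holds in a limited form. Both the event definition and the list of correlated variables are fixed in the protocol article, and together they produce a positive discomfort–adverse-event coefficient with no true link behind it. Multiplicity adjustment does not help, because the coefficient itself is displaced.

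The size depends on how many ratings exceed 7, which is unknown before data. At 5% unrelated other events it runs from about 0.13 (1% of ratings above 7) to about 0.75 (37% above 7), and it is zero if none exceed 7. These figures also assume that the same rating enters both variables. If the correlation used a different time point or an average of ratings, the overlap would be weaker but would not vanish as long as the ratings are related.

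The severity is minor: one exploratory association is affected and the primary analysis is not.

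**What to change.** Add to the Statistical analysis section that, in the associations of adverse events with discomfort and with stimulation intensity, the adverse-event variable omits events that meet only the discomfort > 7 criterion. Keep those events in the safety table and show them on their own line, by condition. The adverse-event criteria and the stimulation procedure stay as they are.

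As a clarification only, the same sentence could state that the correlations are computed within each condition.

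The change costs wording and no data collection. The article reports that recruitment is under way and no results exist, so it can be made before analysis. The downside is fewer events in the exploratory association. If few or no other events occur, the coefficient will be imprecise or cannot be computed, and the report should say so.

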### Ethics and dissemination

This study will be conducted in accordance with Brazilian ethical standards for research involving human subjects and has been approved by the local Coordinating Research Ethics Committee (CAAE: 76562223.2.1001.5461; oppinion number 6.631.794). The study will be conducted at two private hospitals in São Paulo, Brazil.

### Modification of the protocol

Any changes to the protocol—including changes to study objectives, design, patient population, sample size, procedures, or other significant administrative aspects—will require a formal submission and approval by the institution, which also serves as the clinical trial registry.

